## Abstract

**Background::**

Myocardial infarction is 1 of the most serious cardiovascular diseases. Early interventional therapy preserves the cardiac function of patients with myocardial infarction to the greatest extent, but it is far from meeting people's need only limited to cardiac revascularization. It is also necessary to help patients improve their quality of life, exercise tolerance, and reduce the incidence of acute cardiac recurrence as much as possible. All these depend on cardiac rehabilitation (CR) are based on exercise. Early and correct CR helps to improve the patient's heart function and improve living standards. Traditional Chinese exercise Tai Chi as an alternative form of CR has gradually become popular, but it lacks large samples and high-quality clinical studies to verify it. This study aims to explore the effect of Tai Chi on the cardiac function of patients with myocardial infarction, and to provide a strong basis for patients to choose which CR exercise.

**Methods::**

This is a prospective randomized controlled trial. 272 patients with myocardial infarction will be randomly divided into an experimental group and a control group according to 1:1, with 136 cases in each group. The control group: conventional treatment; the experimental group: increase Tai Chi exercise on the basis of the control group. Both groups will receive standard treatment for 24 weeks and will be followed up for 3 months. Observation indicators include: total effective rate, 6 minutes walking test, brain natriuretic peptide, left ventricular ejection fraction, the adverse reaction rate, etc. The data will be analyzed by using SPSS 25.0 software.

**Discussion::**

This study will evaluate the effect of Tai Chi on the cardiac function of patients with myocardial infarction. The results of this test will provide clinical evidence for patients to choose which CR exercise.

**Trial registration::**

OSF Registration number: DOI 10.17605/OSF.IO/QKWDP.

## Introduction

1

With the change in lifestyles, hypertension, hyperglycemia, hyperlipidemia, smoking, lack of exercise, aging of population, and other risk factors, the incidence of coronary heart disease is increasing year by year, and it has become 1 of the main diseases that affect global health.^[1]^ Myocardial infarction is 1 of the cardiovascular diseases with the highest mortality,^[2]^ and it is a serious threat to people's life and health.^[3]^ Early intervention and standardized drug treatment has greatly reduced the mortality of patients with myocardial infarction, but there is a lack of attention to rehabilitation after the onset of disease. Most patients with myocardial infarction fear exercise, resulting in decreased activity tolerance, decreased cardiopulmonary function, anxiety, decreased quality of life, relapsed illness, and often require hospitalization, which brings a heavy burden to the patient's family and society.^[4]^ Therefore, there is an urgent need to find a method that is simple and easy to operate, with less side effects, that can improve patients’ cardiac function and exercise tolerance, thereby improving the quality of life.

Tai Chi, originated in ancient China, is mainly divided into 5 schools: Chen, Yang, Wu, Wu, and Sun. It is divided into 24 styles, 36 styles, and 108 styles. It is a medium-strength defensive exercise,^[5]^ with the characteristics of health care, economy and convenience.^[6,7]^ Studies have found that Tai Chi exercise can increase patient endurance, balance and sensitivity, and improve the quality of life of patients.^[8,9]^ At the same time, moderate-intensity aerobic exercise is the core content of cardiac rehabilitation, which can not only enhance the relative adaptability of heart function, but also improve the blood supply capacity of the coronary artery of the heart to a certain extent, and reduce the cardiovascular mortality rate by 20% to 30%.^[10]^ As an ancient exercise training, Tai Chi has the characteristics of ease and softness, smoothness and unobstructed intention, which is convenient for patients’ participation and persistence. It has advantages for the rehabilitation of patients with myocardial infarction, but there is currently a lack of large sample comparisons in the academic community.

Therefore, we plan to evaluate the efficacy and safety of Tai Chi on the cardiac function of patients with myocardial infarction through this randomized controlled trial.

## Methods

2

### Study design

2.1

This is a prospective randomized controlled clinical trial to study the effect of Tai Chi on the cardiac function of patients with myocardial infarction. This research protocol follows the latest consolidated standards of reporting trials 2017 (See Fig. 1 for the flow chart), and Standard Protocol Items: Recommendations for Interventional Trials 2013 statement (see SPIRIT checklist, Table S1, Supplemental Digital Content).

**Figure 1 F1:**
[figure not shown]
Flow diagram of study. 6MWT = 6 minutes walking test, BNP = brain natriuretic peptide, LVEF = left ventricular ejection fraction, SF-36 = short-form36.

### Ethics and registration

2.2

This research protocol complies with the Declaration of Helsinki and was approved by the clinical research ethics committee of our hospital. This study has been registered in open science framework (OSF) with registration number of DOI 10.17605/OSF.IO/QKWDP. Before randomization, all patients need to sign a written informed consent and they are free to choose whether to continue the trial at any time.

### Patients

2.3

Diagnostic criteria: ① Diagnosis of myocardial infarction in the fourth edition of the General Definition of Myocardial infarction in the European Society of Cardiology 2018^[11]^; ② According to the New York Heart Association (NYHA) cardiac function classification standard, cardiac function is grade I to III.

Inclusion criteria: ① Meet the diagnostic criteria for myocardial infarction; ② Age ≥35 years old and ≤80 years old; ③ Cardiac function grade I to III; ④ Stable condition after interventional surgery without serious complications; ⑤ Have a certain communication and understanding ability, express their wishes correctly; ⑥ After informed consent and signed an informed consent form, they voluntarily participated in this research project.

Exclusion criteria: (A standard for judging whether a patient can become a experimental object): ① Suffer from acute systemic disease; ② Cardiac function grade IV; ③ Risk stratification of cardiac rehabilitation in patients with coronary heart disease^[12]^ showed that they are at high-risk; ④ Relative or absolute contraindications for rehabilitation exercise such as blood pressure drop during exercise; ⑤ Limb dysfunction; ⑥ Complicated with severe mental illness; ⑦ Unable to understand the research plan after explanation or unwilling to participate.

Exclusion criteria: (A criterion used to screen patients who have become experimental subjects, but the relevant data cannot be included in the final data analysis): ① Severe adverse events or serious complications are not suitable for the next test; ② Poor compliance, which affects the judgment of efficacy and safety; ③ The disease progresses during the treatment process, and the treatment plan needs to be changed; ④ For any reason, the subject asked to withdraw from the trial.

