### Sample size

2.4

According to the calculation formula:

$${\text{n}}_{1}=\pi (1-\pi ){\left[\frac{\left(\mu_{1-\alpha }+\mu_{1-\beta }\right)}{\delta }\right]}^{2}\frac{\left(1+\text{c}\right)}{\text{c}},{\text{n}}_{2}=\text{c}{\text{n}}_{1}$$

Using the superiority test, $\mu_{1-\alpha }=1.64,\mu_{1-\beta }=1.28.\pi =0.8,c=1,\delta =0.15$, calculate n1 = n2 = 122. Considering the clinical dropout rate of about 10%, a total of 272 cases need to be included. The included patients will be numbered according to the order of visits, and will be divided into an experimental group and a control group using a completely random method, with 136 cases in each group.

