#### Efficacy indicators

2.6.1

Main efficacy indicators: total effective rate: referring to the “Guiding Principles for Clinical Research of New Chinese Medicines”,^[13]^ total effective rate = (marked effective number + effective number)/total number × 100%. According to NYHA grading method, evaluate the curative effect of cardiac function: ① Marked effective: cardiac function improved by more than grade 2; ② Effective: cardiac function improved by grade 1, but not as good as grade 2; ③ Ineffective: cardiac function improved less than grade 1; ④ Deterioration: the deterioration of heart function is less than grade 1.

Secondary efficacy indicators: 6 minutes walking test, brain natriuretic peptide, left ventricular ejection fraction, medical outcomes study short-form36 (SF-36).

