### Statistical analysis plan

2.9

The database is established by Excel. The full analysis set refers to the intent-to-treat analysis of all subjects randomly enroll, treat at least once and visit at least once. Per-protocol set: includes all subjects who comply with the trial protocol, have no missing baseline variables, and can measure the main variables. safety set: including random enrollment, at least 1 medication, and at least 1 safety visit after medication.

In this study, SPSS25.0 statistical analysis software will be used for data analysis. If the measurement data meet the normal distribution, the independent sample *t* test is used between the groups, and the paired sample *t* test is used within the group. The results are represented by ($\bar{X}\pm S$); Nonparametric test will be used for those who did not meet the normality, and the results will be expressed in quartiles; Chi square test will be used for counting data. The incidence of adverse events will be compared by chi square test. *P* *<* *.05*, with statistical significance.

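### NYHA class I patients are eligible and counted in the primary response rate but cannot respond, so a class I share above 5% to 20% (depending on what π denotes) makes the planned 80% rate with a 15-point difference impossible, and smaller shares can cost power

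*Protocol article*

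**What the plan says.** Section 2.3 (Patients) makes class I eligible twice, in the diagnostic criteria and in inclusion criterion 3: "Cardiac function grade I to III".

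Section 2.6.1 (Efficacy indicators) defines the primary endpoint as "total effective rate = (marked effective number + effective number)/total number × 100"%. The lowest category that counts as a response is "Effective: cardiac function improved by grade 1, but not as good as grade 2". Anything short of that falls under "Ineffective: cardiac function improved less than grade 1" or deterioration.

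Section 2.4 (Sample size) uses π = 0.8, δ = 0.15 and standard normal values of 1.64 and 1.28 to "calculate n1 = n2 = 122". It then adds dropout: "Considering the clinical dropout rate of about 10%, a total of 272 cases need to be included". It does not say whether π is the mean, control or experimental rate, and it makes no allowance for baseline class.

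Section 2.9 (Statistical analysis plan) sets no baseline NYHA condition: "The full analysis set refers to the intent-to-treat analysis of all subjects randomly enroll, treat at least once and visit at least once". No section caps the number of class I patients, stratifies on class, or gives class I patients a separate response rule.

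**The concern.** A class I patient has no better grade to move to. Under the stated categories such a patient is ineffective or deteriorated whatever the treatment does, yet still counts in the denominator. The eligibility rule, the endpoint formula and the planning rates are all fixed in this article, and they do not fit together.

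The stake is the chance of detecting an effect on the primary endpoint. Certain failures in both arms put a ceiling on the attainable rate and shrink the difference between arms. Over the shares considered here they also move the rates towards 50%, where the binomial variance is larger.

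**Working it through.** **Inputs.** From section 2.4: z = 1.64 (one-sided 5%), z = 1.28 (90% power), π = 0.80, δ = 0.15, c = 1, 122 evaluable per arm, 10% dropout. From 2.3 and 2.6.1: class I is eligible and the denominator is all patients. The class I share f is not given, so it is an assumption, shown from 5% to 30%.

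**Step 1: the plan's own figure.** n = 0.8 × 0.2 × [(1.64 + 1.28)/0.15]² × 2 = 0.16 × 378.95 × 2 = 121.26, rounded up to 122. With dropout, 122/0.9 = 135.6, rounded up to 136 per arm, 272 in total. Both figures reproduce.

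**Step 2: the ceiling.** Overall rate = (1−f) × rate in class II–III, which is at most 1−f. The higher planned rate must not exceed this.

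| Reading of π = 0.80 | Control vs experimental | Largest f at which the pair is possible |
|---|---|---|
| Mean rate | 72.5% vs 87.5% | 12.5% |
| Control rate | 80% vs 95% | 5% |
| Experimental rate | 65% vs 80% | 20% |

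**Step 3: the difference alone.** Overall difference = (1−f) × difference in class II–III. A 15-point overall difference therefore needs 0.15/(1−f) in class II–III: 15.8 points at f = 5%, 16.7 at 10%, 18.8 at 20% and 21.4 at 30%. That is harder to reach but not impossible.

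**Step 4: power with all patients counted.** Assume that 72.5% versus 87.5% holds in class II–III only, with 122 per arm. Power = Φ{[(p₂−p₁) − z·SE₀]/SE₁}, where SE₀ = √[2p̄(1−p̄)/n] and SE₁ = √{[p₁(1−p₁) + p₂(1−p₂)]/n}. For f = 20%: p₁ = 0.58, p₂ = 0.70, p̄ = 0.64, SE₀ = 0.0615, SE₁ = 0.0610, so (0.12 − 1.645 × 0.0615)/0.0610 ≈ 0.31 and power is 62%.

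**Step 5: power with class II–III only.** The same formula, with 122 × (1−f) per arm and rates 72.5% versus 87.5%.

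| f | Overall rates | Difference (points) | Power, all patients | n per arm, class II–III | Power, class II–III |
|---|---|---|---|---|---|
| 0 | 72.5% vs 87.5% | 15.0 | 90% | 122 | 90% |
| 5% | 68.9% vs 83.1% | 14.2 | 84% | 116 | 89% |
| 10% | 65.2% vs 78.7% | 13.5 | 76% | 110 | 88% |
| 20% | 58.0% vs 70.0% | 12.0 | 62% | 98 | 84% |
| 30% | 50.7% vs 61.2% | 10.5 | 50% | 85 | 79% |

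Power is one-sided at 5%, as in section 2.4. At a two-sided 5% level the all-patient column reads 84%, 74%, 65%, 50% and 38%.

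**Step 6: dependence on the reading of π.** At f = 20% the all-patient one-sided power is 62% under the mean-rate reading, 66% under the control-rate reading and 60% under the experimental-rate reading. The reading matters more for the ceiling than for the loss of power.

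**The case against.** The strongest reply is that the size of the problem rests on an input the article does not give. Class I is eligible, but nothing says it will be common, and at a 5% share the one-sided loss is modest (90% to 84%). That stands. Section 2.3 asks for stable patients after intervention without serious complications and excludes class IV and high-risk patients. This makes a material class I share plausible but does not establish one.

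A second reply is that π = 0.80 may already describe the mixed population. If so, nothing is diluted while f stays below the ceiling. The article does not settle this. That reading is demanding, though: at f = 10%, 72.5% versus 87.5% overall needs 0.725/0.9 = 80.6% versus 0.875/0.9 = 97.2% in class II–III. Above the ceiling it cannot rescue the plan.

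Third, the response categories come from a cited guideline that is not available here and might treat class I separately. The article's own formula does not.

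A reader might also infer three stronger things that the documents do not support:
- **That a 15-point difference is itself out of reach.** Only the rate is capped. What becomes impossible is the pair of 80% and 15 points.
- **That 72.5% versus 87.5% is the plan's stated assumption.** It is one of three readings of π.
- **That a null result would be uninterpretable, or the comparison biased.** Certain non-responders in both arms of a randomised trial do not bias the comparison or inflate the type I error. The confidence interval could still be read; the trial would be less sensitive.

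**Conclusion.** The inconsistency is real and follows from the text alone: an eligible group cannot meet the primary endpoint but counts in its denominator. The ceiling of 1−f is pure arithmetic and holds at any share, with thresholds of 5%, 12.5% or 20% according to what π denotes.

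The loss of power is conditional. It assumes a class I share, and it assumes that the planned rates apply to class II–III patients only. On those terms one-sided power drops by roughly 7 points at a 5% share and to about half at 30%. The consequence is lower power and sensitivity on the primary endpoint. It should be settled before outcome data are seen.

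**What to change.** In sections 2.6.1 and 2.9, define the primary analysis of the total effective rate on randomised patients in NYHA class II–III at baseline. Class is fixed before randomisation, so the comparison stays unbiased. Keep class I patients for the 6-minute walk test, BNP, LVEF, SF-36 and safety. In section 2.4, state which rate π denotes and restate the power for the expected number of class II–III patients.

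The text change is small, but it has costs. The primary set is smaller and the primary conclusion is limited to class II–III. At the current size the restricted analysis has more power than the all-patient one (88%, 84% and 79% against 76%, 62% and 50% at shares of 10%, 20% and 30%) but stays below the planned 90%. Keeping 90% needs 122 evaluable class II–III patients per arm. That is 122/[(1−f) × 0.9] randomised per arm: 151, 170 and 194, or 302, 340 and 388 in total, at those shares. Leaving the denominator unchanged would need about 420, 608 and 850 by the plan's formula.

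Re-deriving π and δ for the expected class mix, or defining response for class I patients, would also remove the contradiction. A proportional-odds analysis of week-24 NYHA class adjusted for baseline class can use every patient and is an optional supportive analysis.

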### Interventions

2.5

This study will select patients who meet the criteria of this study by recruiting in the hospital. A randomized controlled study will be used, in which the control group: conventional treatment; the experimental group: Tai Chi exercise will be added to the control group. The 2 groups of patients will receive the same routine care. During the trial period, avoid smoking, alcohol and irritating food, avoid strenuous exercise, and pay attention to adverse reactions. When necessary, the attending doctor can appropriately adjust the plan according to the patient's condition, and all intervention methods will be recorded in detail for the final result analysis. Efficacy assessors are not aware of the study group plan, and data statisticians are not involved in the design and implementation of the study. Before and after treatment, the health status of each patient will be evaluated, including the outcome indicators, and all patients will be followed up by telephone. Follow-up content includes cardiovascular events and rehospitalization.

Control group: according to the relevant guidelines after myocardial infarction intervention, standard drug treatments will be given, including antiplatelet drugs, statins, angiotensin converting enzyme inhibitors, nitrates, β-receptor blockers, and health education. The content of the education includes the control of myocardial infarction risk factors, techniques for improving sleep quality, diet guidance, etc, and pays attention to communicating with patients, mastering their psychological and emotional changes, and avoiding or alleviating bad moods such as anxiety and depression in elderly patients.

Experimental group: on the basis of conventional treatment, the experimental group will be given 24 simplified Tai Chi. Professional Tai Chi teachers will teach and practice the subjects to ensure that the practice time and movement rhythm are basically the same. The whole set of Tai Chi includes 3 parts: preparation activity, training activity and end activity, totaling about 20 minutes, twice a day, once in the morning and once in the afternoon, and lasts for 24 weeks.

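### Section 2.3 bars enrolled patients from the final analysis for post-enrolment reasons plausibly tied to outcome, contradicting the intent-to-treat set in section 2.9; the primary result can be biased, in a direction the protocol does not establish

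*Protocol article*

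**What the plan says.** Section 2.3 (Patients) of the protocol article has two exclusion lists. The first governs entry. The second is introduced as "A criterion used to screen patients who have become experimental subjects, but the relevant data cannot be included in the final data analysis" and gives four reasons:

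- "Severe adverse events or serious complications are not suitable for the next test"
- "Poor compliance, which affects the judgment of efficacy and safety"
- "The disease progresses during the treatment process, and the treatment plan needs to be changed"
- "For any reason, the subject asked to withdraw from the trial"

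No threshold for poor compliance is given, and the list is not tied to any named analysis set.

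Section 2.9 (Statistical analysis plan) defines three sets. For the first: "The full analysis set refers to the intent-to-treat analysis of all subjects randomly enroll, treat at least once and visit at least once". For the second: "Per-protocol set: includes all subjects who comply with the trial protocol, have no missing baseline variables, and can measure the main variables". The third, the safety set, needs randomisation, at least one medication and at least one later safety visit. None of the three definitions refers to the list in section 2.3, and section 2.9 does not say which set carries the primary analysis.

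The primary outcome (section 2.6.1) is the total effective rate, a binary measure of improvement in NYHA class.

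**The concern.** Randomisation makes the arms comparable only if patients are analysed whatever happens to them afterwards. Each reason in the second list arises after enrolment and plausibly relates to how the patient fared: harm, intolerance, deterioration, or giving up. If such patients are removed, the effective rate among those left is likely to exceed the rate among all randomised. If the arms lose different numbers, or different kinds, of patients, the difference between arms is distorted too.

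The protocol also gives two incompatible instructions. An analyst could follow section 2.3 or section 2.9 and claim adherence either way. Because poor compliance has no threshold, part of that choice could be made after the data are seen.

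Read literally, the rule reaches safety as well: the first reason on the list would take out the severe cases that the safety set should contain.

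**Working it through.** **1. The sections side by side.** Take a patient randomised, treated, seen at week 12, who has a severe adverse event at week 16. Under section 2.9 the patient is in the full analysis set (randomised, treated, visited) and, given one safety visit, in the safety set. Under section 2.3 the patient's data may not enter the final analysis. The same conflict holds for a poor complier, a patient who progresses, or one who withdraws after a visit. Section 2.9 has a separate per-protocol set to which such a list would naturally belong, but no sentence makes that link.

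**2. The plan's own figure.** Section 2.4 uses n = π(1−π)[(1.64+1.28)/δ]²(1+c)/c with π = 0.8, δ = 0.15, c = 1:

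0.16 × (2.92/0.15)² × 2 = 121.3, rounded up to 122 per group; 122/0.9 = 135.6, rounded up to 136; total 272. This reproduces. The 1.64 and 1.28 correspond to one-sided 5% and 90% power, and the inflation treats about 10% of patients as lost to analysis.

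**3. Size of the possible bias.** From the protocol: 136 per arm and δ = 0.15. Assumed: no true effect; a true rate p = 0.725 in both arms (the control rate if π = 0.8 is the average of two rates 0.15 apart, 0.8 − 0.075); and the exclusion fractions e. The protocol gives no arm-specific fractions. With r the response rate among those excluded, the rate among those retained is

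(p − e·r)/(1 − e).

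For e = 0.15 and r = 0: 0.725/0.85 = 0.853. For e = 0.05: 0.725/0.95 = 0.763. Difference: +0.090.

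| Excluded, Tai Chi / control | r | Apparent rates | Spurious difference |
|---|---|---|---|
| 15% / 5% | 0 | 85.3% vs 76.3% | +9.0 points |
| 10% / 5% | 0 | 80.6% vs 76.3% | +4.2 points |
| 10% / 10% | 0 | 80.6% vs 80.6% | 0 |
| 5% / 15% | 0 | 76.3% vs 85.3% | −9.0 points |
| 15% / 5% | 0.35 | 79.1% vs 74.5% | +4.6 points |
| 15% / 5% | 0.725 (unrelated to outcome) | 72.5% vs 72.5% | 0 |

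In the first row, 136 × 0.85 = 115.6 and 136 × 0.95 = 129.2 patients remain. The standard error of the difference is √(0.853×0.147/115.6 + 0.763×0.237/129.2) ≈ 0.050, so the expected z is about 1.80. The chance of a two-sided p below 0.05 is then about 43% (42% with a pooled and 44% with an unpooled standard error), against a nominal 5%. With r = 0.35 it is about 14%.

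The 10%/10% row shows no difference between arms, yet both rates are still overstated by 8.1 points (80.6 − 72.5).

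**4. Power if these patients are kept.** Assume 10% per arm have no week-24 class and count as not effective. With π as the average rate, 0.725 vs 0.875 become 0.6525 vs 0.7875 (each × 0.9). At 136 per group one-sided power is about 80%, against about 90% for 122 evaluable per group at the full rates. If π = 0.8 is instead the control rate (0.80 vs 0.95, becoming 0.72 vs 0.855), power at 136 is about 86%.

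**The case against.** **Direction.** A reader might infer that the rule favours Tai Chi. The document does not support that as a fact. It gives no exclusion rates by arm. Serious complications and progression could be commoner under conventional treatment alone, and removing those patients would work against Tai Chi. The table shows both signs and zero. This objection stands.

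**Compliance.** It is tempting to say that only Tai Chi patients can comply poorly. Section 2.5 gives both arms standard drugs and education, and its advice on smoking, alcohol, food and strenuous exercise is not limited to one arm. Controls can be non-compliant too. What remains is that one arm carries an extra daily burden.

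**Early losses.** One might add that patients lost before week 12 vanish from the full analysis set. That needs its visit requirement to mean a post-baseline visit, which section 2.9 does not say; section 2.7 also collects data before treatment. Requiring one treatment and one visit is a common modified intent-to-treat definition.

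**Section 2.5.** Plan adjustments by the attending doctor might seem to clash with the progression criterion. But section 2.5 says only that "all intervention methods will be recorded in detail for the final result analysis"; it does not promise that every patient with an adjusted plan stays in the analysis. The two can coexist.

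**Safety.** It is too strong to say that the adverse-event comparison will lose its severe cases. Section 2.9 keeps a separate safety set without such an exclusion, and section 2.8 sends all adverse events for review. The passages are unreconciled, no more.

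**Unseen SAP.** A fuller document might say that the list defines the per-protocol set. That does not answer the conflict: this is a rule stated without limit that contradicts another stated rule, not a missing detail.

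**Conclusion.** The contradiction between sections 2.3 and 2.9 holds on the text alone and needs no assumption. Applying the section 2.3 rule can bias the primary comparison. A lean towards Tai Chi is plausible, because only that arm has a programme of about 20 minutes twice a day for 24 weeks, but it is not shown.

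Under the stated assumptions the spurious difference runs from −9.0 to +9.0 points, that is, up to 60% of the planned 15 points (9.0/15). It vanishes when exclusions are equal in number and outcome, or unrelated to outcome. The exclusion fractions, the response rate among those excluded and the 72.5% are assumptions; the protocol gives only about 10% dropout overall and does not say whether π is the average or the control rate.

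It must be corrected before analysis, because the primary result depends on which section is followed.

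**What to change.** 1. State in section 2.3 that the second list applies only to the per-protocol set, and reconcile it with section 2.9. It should remain an analysis-set definition; this point does not call for turning it into rules for stopping treatment.
2. Name as primary the analysis of all randomised patients in the arm assigned. Count a missing week-24 NYHA class, including through death, as not effective. Keep the per-protocol analysis as supportive.
3. State that all severe adverse events stay in the safety analysis.
4. Restate the power for this primary analysis.

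The cost is mostly wording, plus week-24 assessment, at a visit already scheduled, of patients who have left the intervention but still agree to be seen. Effective rates will be lower than in a selected set. If 10% per arm are missing and counted as not effective, one-sided power at 136 per group is about 80% with π as the average rate (86% with π as the control rate). Holding 90% would take about 188 per group (156 with π as the control rate); otherwise the lower power should be stated openly.

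### Section 2.3 bars the data of patients stopped for severe adverse events from the final analysis, the safety set in 2.9 keeps them, and the adverse-event test does not say which rule applies

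*Protocol article*

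**What the plan says.** Section 2.3 of the protocol article has two exclusion lists. The first screens candidates. The second is headed "A criterion used to screen patients who have become experimental subjects, but the relevant data cannot be included in the final data analysis". Its first item is "① Severe adverse events or serious complications are not suitable for the next test". The English is rough, but the natural meaning is a patient whose severe event or serious complication makes it unsuitable to go on. The remaining items cover poor compliance, progression that requires a changed treatment plan, and withdrawal on request. Nothing in the list separates efficacy data from safety data.

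Section 2.9 defines its sets on other terms. The full analysis set is given as "The full analysis set refers to the intent-to-treat analysis of all subjects randomly enroll, treat at least once and visit at least once". The safety set is described as "including random enrollment, at least 1 medication, and at least 1 safety visit after medication". Neither definition removes a patient for a severe event, and neither refers to the second list. On the test itself, 2.9 says "The incidence of adverse events will be compared by chi square test" and names no set. Section 2.6.2 defines the adverse reaction rate as any uncomfortable symptom during treatment. Section 2.8 sends all adverse events to the ethics committee and sets up a monitoring board.

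**The concern.** The introduction and the discussion both name safety as an aim. The patients have had an infarction and are to exercise twice a day for 24 weeks. A rule that drops a patient's data because of a severe adverse event selects on the very outcome that the safety comparison should measure. Each such patient is lost from the count of events and from the count at risk. The arm with more severe events loses more, so a real excess in either arm would be partly or almost wholly hidden. Because the article supports two opposite treatments of the same patient, the choice could also be made after the results are known.

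**Working it through.** **Step 1. The two rules applied to one patient.** Take a randomised, treated patient who has a severe adverse event, has a safety visit afterwards, and is judged unfit to continue.

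- Under 2.3, second list, item 1: the patient's data are out, since "but the relevant data cannot be included in the final data analysis" governs every item in the list.
- Under 2.9, safety set: the patient is in.
- Under 2.9, full analysis set: the patient is in, given one visit.
- Chi-square test of adverse events: no set is named, so the text does not say which answer applies.

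The list cannot simply be read as concerning efficacy only: its second item removes poor compliers on the ground that they disturb the judgment of both efficacy and safety.

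**Step 2. Arm size, from section 2.4.** The inputs are 1.64, 1.28, π = 0.8, δ = 0.15 and c = 1.

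n = 0.8 × 0.2 × [(1.64 + 1.28)/0.15]² × 2 = 121.26, rounded up to 122. With 10% dropout, 122/0.9 = 135.6, rounded up to 136 per arm and 272 in total. The plan's figures reproduce, and 136 per arm is used below.

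**Step 3. Direction of the effect.** In one arm of N patients, let s be those excluded under item 1 and o those with other adverse events only.

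- Rate with everyone kept: (o + s)/N
- Rate after item 1 is applied: o/(N − s)

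The first minus the second equals s(N − s − o)/[N(N − s)]. This is positive whenever s > 0 and some patients have no event. The rate therefore falls in each arm that has any such exclusion, not only in the worse arm. Events that led to exclusion under item 1 are counted as zero in both arms by construction.

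**Step 4. Size, under assumed counts.** The documents give no event rates, so s and o are assumptions (Tai Chi v control, 136 per arm).

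| s | o per arm | All kept | Difference | After item 1 | Difference |
|---|---|---|---|---|---|
| 3 v 1 | 14 | 17/136 v 15/136 = 12.5% v 11.0% | 1.47 | 14/133 v 14/135 = 10.53% v 10.37% | 0.16 |
| 7 v 3 | 14 | 21/136 v 17/136 = 15.4% v 12.5% | 2.9 | 14/129 v 14/133 = 10.9% v 10.5% | 0.3 |
| 14 v 7 | 14 | 28/136 v 21/136 = 20.6% v 15.4% | 5.1 | 14/122 v 14/129 = 11.5% v 10.9% | 0.6 |
| 14 v 4 | 27 | 41/136 v 31/136 = 30.1% v 22.8% | 7.4 | 27/122 v 27/132 = 22.1% v 20.5% | 1.7 |
| 7 v 7 | 14 | 21/136 in both = 15.4% | 0 | 14/129 in both = 10.9% | 0 |

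Differences are in percentage points, taken from unrounded rates. In the four unbalanced rows, at least three quarters of the difference disappears (7.35 to 1.68 in the mildest case, a loss of 77%). With a balanced split, both rates fall but a difference in other events is hardly touched: a gap of 6 patients would go from 6/136 = 4.4 points to 6/129 = 4.7 points.

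**The case against.** The strongest answer is that 2.9 already contains a rule written for safety data. The safety set is the more specific provision, it has no removal for severe events, and the protocol nowhere says that 2.3 overrides it. The second list also resembles reasons for leaving a per-protocol set, and the data it refers to are not defined. Section 2.8 monitors every participant and collects all adverse events. A reader might infer from 2.3 that the trial will leave its worst harms out of the comparison, or means to. The documents do not support that: the harms are lost only if 2.3 governs, and the safety set points the other way. This part of the objection stands.

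It does not remove the conflict. The list's scope is the final data analysis as a whole, and 2.9 defines its per-protocol set without using the list. Reporting events to a committee or a board does not decide who is counted in the published comparison. Leaving the choice of set to a separate analysis plan would be ordinary, but no analysis plan can obey both sections as they are written.

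The objection about size also stands in part. All counts are assumed, and the unbalanced rows all put the excess in the Tai Chi arm. The row with 14 exclusions in 136 (10.3%) would by itself use up the whole 10% dropout allowance, in a trial that screens out high-risk patients. The planned test would not change its conclusion in that 14 v 4 row either: p is 0.17 with all patients kept. A split of 10 v 3 severe events alone gives p = 0.047 without continuity correction but 0.088 with it and 0.085 by Fisher's exact test, and no separate test of severe events is planned. The case therefore rests on the distortion of the estimate, not on a significance result.

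**Conclusion.** Wrong as written. Section 2.3 bars the data of patients stopped for severe adverse events or serious complications, without a safety exception; section 2.9 keeps them in the safety set once they have a later safety visit; and the adverse-event test is tied to neither rule. Following 2.3 would condition the harm comparison on the harm, lower the rate in every arm with such exclusions, and shrink any between-arm difference in severe events. The illustrated loss runs from 1.47 to 0.16 points at the low end to 7.4 to 1.7 points at the high end, with little or no change in the difference when exclusions are balanced. These sizes depend on assumed counts. The contradiction and the direction of the effect do not.

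**What to change.** Reconcile the two sections.

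- In 2.3, state that item 1 of the second list does not remove a patient from the safety analysis; it may limit the per-protocol set only.
- In 2.9, state that the adverse-event comparison uses the safety set, that every patient meeting item 1 is kept in the randomised arm with the event counted, and that severe events are tabulated by arm.

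Deleting the barring clause from the heading would go further than this point supports, because it also governs items 2 to 4. Nor should item 1 be worded so that follow-up of these patients ends, since their harms still have to be recorded. The clinical rules for stopping the intervention are left as they are.

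The cost is two sentences. No new data are needed, because 2.8 already collects all adverse events. The reported adverse-event rate may be less favourable. The change should be made before any outcome data are seen by arm.
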